## Methods

### Study purpose

(1) Primary purpose: To investigate neurologic function in the early postoperative period for patients with supratentorial intracranial gliomas under inhalational general anesthesia compared to intravenous general anesthesia. The hypothesis is that the difference in postoperative National Institute of Health Stroke Scale (NIHSS or modified NIHSS) score changes under the two general anesthesia methods are not different, with the score difference within − 1 to 1.

(2) Secondary purpose: To compare the effects of inhalational general anesthesia versus intravenous general anesthesia on neurocognition, hemodynamics, cerebral physiology, anesthesia recovery quality, pain scores, anesthesia expenses, and stress responses in patients with supratentorial intracranial gliomas undergoing elective craniotomy.

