### Trial design

The study is a prospective, single-center, open label, randomized parallel arm equivalent clinical trial comparing sevoflurane and propofol, both combined with remifentanil, general anesthesia (Sevoflurane-remifentanil versus Propofol-remifentanil group) in patients with supratentorial gliomas; it will be carried out in the neurosurgical operation room in Beijing Tiantan Hospital (a large city), Capital Medical University, Beijing, China.

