### Study endpoint

The primary endpoint will be NIHSS score change within 4 h after general anesthesia by sevoflurane-remifentanil or propofol-remifentanil when observer’s assessment of alertness/sedation (OAA/S) reaches 4. The time to reach OAA/S score of 4 at the first time point will be recorded.

Secondary endpoints will be as follows:
The NIHSS score change at postoperative day 1 and postoperative day 2 from the baseline, the level of OAA/S in these two time points will be recorded.Hemodynamic stability including blood pressure, heart rate, episodes of hypertension, hypotension, tachycardia, and bradycardia;Intraoperative brain relaxation (Brain relaxation assessed immediately after opening of the dura on a scale ranging from 1 to 4 (1 = perfectly relaxed, 2 = satisfactorily relaxed, 3 = firm brain, 4 = bulging brain);Quality of anesthesia emergence including time of eye opening, time of emergence, coughing during extubation, postoperative nausea and vomiting (PONV), shivering, and agitation;Quality of anesthesia recovery assessed by QoR-40 at postoperative day 2;Changes of cognitive function at postoperative day 2 assessed by MMSE;Postoperative pain at PACU, 1, and 2 days after surgery evaluated by VAS;Postoperative neurological complications (e.g., intracranial hematoma, infection, seizure etc.);Anesthesia expenses and in-hospital total expenses;

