### Sample size calculation

Sample size calculation was conducted by PASS software (NCSS, LLC, USA). The mean difference of NIHSS change between the two types of anesthetics was estimated as 0.5, the estimated within group standard deviation was 1.5, and 1.0 was set as the equivalent margin based on clinical significance. Z-test was used as power analysis of equivalence tests of two independent proportions to detect equivalence. The minimum number of cases was 160 per group to achieve 80% power to detect a possible equivalence between the two groups. Considering the possibility of early termination during the study and allowing for a 10% drop-out rate, this number was raised to 176 subjects for each group. As two groups were to be studied, we aim to enroll 352 subjects.

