### Statistical analysis plan

Kolmogorov-Smirnov testing will be used for evaluating if the continuous variables have a normal distribution or not. Descriptive statistics will be reported as means with standard deviation for normally distributed data; medians with interquartile range will be described for non-normally distributed data; for categorical variables, count (percentage) will be described. The difference in postoperative NIHSS scores at certain time points between the propofol and sevoflurance groups will be analyzed by t-test or Mann-Whitney U test depending on normal or non-normal distribution, respectively, and 95% confident interval will be determined for the NIHSS score change and difference between the two groups. The changes in VAS scores, intraoperative parameters, and stress response biomarkers over the observation time will be compared using repeated measurement, and post hoc analysis will be used for sensitivity analysis. For other secondary outcomes such as brain relaxation, MMSE score, anesthesia quality score and medical expense, the difference between the two groups will be analyzed by t-test or Mann-Whitney U test. All the categorical variables will be analyzed by chi-square testing. Missing data will be adjusted using inverse probability weighting and worst-case imputation scenarios. Statistical significance is defined as a type I error of 0.05, and the nature of the testing is two-tailed. Analyses will be conducted using Statistical Package for the Social Sciences (SPSS) version 17.0 (Chicago, IL, USA).

All data will be analyzed according to an intent-to-treat, such that all randomized patients originally allocated to the propofol or sevoflurane anesthesia arm at the time of randomization will be used for efficacy analysis. No interim analysis is planned. Worst observation carried forward method will be used to handle missing data.

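### The analysis section leads with a test of difference for NIHSS and never ties its planned 95% confidence interval to the ±1 equivalence margin

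*Protocol article*

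**What the plan says.** Four parts of the protocol article set up an equivalence question about a mean difference in change:

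- Trial design calls the study a "randomized parallel arm equivalent clinical trial".
- Study purpose states the hypothesis that the NIHSS changes in the two groups "are not different, with the score difference within − 1 to 1".
- Study endpoint: "The primary endpoint will be NIHSS score change within 4 h after general anesthesia", measured once the patient reaches an OAA/S of 4.
- Sample size calculation: "The mean difference of NIHSS change between the two types of anesthetics was estimated as 0.5", with a within-group SD of 1.5, and "1.0 was set as the equivalent margin based on clinical significance".

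The Statistical analysis plan section then says that the difference in postoperative NIHSS between groups "will be analyzed by t-test or Mann-Whitney U test depending on normal or non-normal distribution", with normality judged by a Kolmogorov-Smirnov test. It adds: "Statistical significance is defined as a type I error of 0.05, and the nature of the testing is two-tailed". The sentence that names these tests also plans a 95% confidence interval for the NIHSS change and for the difference between groups. The section mentions neither the margin nor a rule for declaring equivalence.

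**The concern.** The t-test and the Mann-Whitney test both take no difference as the null hypothesis. A non-significant result does not show that the difference is smaller than 1, and a significant result does not show that it is larger. The planned interval could answer the question, but the section does not connect it with ±1. The report could therefore carry a p-value and an interval that point to different headlines, with the choice between them made after the data are seen.

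The normality check adds a second problem. The margin and SD in the sample size calculation refer to a difference in means. If the check sends the analysis to Mann-Whitney, the named test no longer concerns that quantity, and it is unclear whether the interval is still one for the mean difference.

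**Working it through.** **Inputs** (Sample size calculation unless noted): true difference 0.5; SD 1.5; margin 1.0; 160 per group; power 80%. Two-tailed 0.05 and the 95% interval come from the Statistical analysis plan section. No alpha is given for the sample size.

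**The plan's own figure.** For two one-sided tests on means, n per group = 2·SD²·(z for alpha + z for power)² / (margin − difference)².

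- One-sided 0.025 (a 95% interval): 2 × 2.25 × (1.960 + 0.842)² / 0.5² = 18 × 7.85 = 141.3, so 142.
- One-sided 0.05 (a 90% interval): 18 × (1.645 + 0.842)² = 111.3, so 112.

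The stated 160 is not reproduced at 80% power by either; it is close to the 162 needed for 85% power at one-sided 0.025. For the present point it matters only that 160 exceeds what a margin-based analysis needs.

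**Standard error.** SE = 1.5 × √(2/160) = 0.1677.

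**When each result occurs** (positive direction).

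- The difference test is significant once the estimate exceeds 1.96 × 0.1677 = 0.329.
- The 95% interval lies inside ±1 while the estimate is below 1 − 0.329 = 0.671.
- Both occur together when the estimate lies between 0.329 and 0.671.

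**At the planning difference of 0.5.**

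- Significant difference: Φ(0.5/0.1677 − 1.96) = Φ(1.02) = 84.6%.
- Interval inside ±1: Φ((1 − 0.5)/0.1677 − 1.96) = 84.6%. The two agree because 0.5 is midway between 0 and the margin.
- Both: Φ(1.02) − Φ(−1.02) = 69.3%.

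| True difference | Difference test significant | 95% interval inside ±1 | Both |
|---|---|---|---|
| 0 | 5.0% | over 99.9% | 5.0% |
| 0.25 | 32.0% | 99.4% | 31.4% |
| 0.5 | 84.6% | 84.6% | 69.3% |
| 0.75 | 99.4% | 31.9% | 31.3% |

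With a 90% interval at a difference of 0.5, power is 90.9% and both occur in 75.6%. With 176 per group and a 95% interval, both occur in 75.7%.

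**The opposite error.** If p > 0.05 were read as equivalence when the true difference is 1.0, the error rate at SD 1.5 would be under 0.01%. It would be 15% at SD 3 and 39% at SD 4; those two SDs are assumptions, not protocol figures.

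**The normality check.** The Appendix shows NIHSS as a sum of integer items. In 2,000 simulated samples of 160 (normal, mean 0.5, SD 1.5, rounded to integers; an assumption about shape), the Kolmogorov-Smirnov test rejected normality in 100%. Mann-Whitney is therefore the likely branch.

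**The case against.** The strongest reply is that the needed interval is already planned. Study purpose gives the region and the analysis section gives the 95% interval for the difference. If that interval concerns means and is read against ±1, it is a valid equivalence analysis (two one-sided tests at 0.025) with 84.6% power at 160 per group. That stands. A reader might infer that the plan cannot support an equivalence claim, or leaves no valid decision on the primary question; the planned interval means the document does not support that.

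Second, a fuller analysis plan may exist, and the NIHSS sentence covers several time points without calling the test the sole primary criterion. Details such as the interval method may properly sit elsewhere. But this section names its test, alpha and sidedness, and the named test answers a different question from the stated hypothesis. That is a stated mismatch, which is more than missing detail.

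Third, a significant p-value with an interval inside ±1 is no logical contradiction: it indicates a small difference within the margin. That also stands. The fault is that no rule says which result governs. Nor is the conflict frequent everywhere: near a true difference of 0 it occurs in about 5% of trials.

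A reader might go further and build a case in which Mann-Whitney misses a mean difference of 1.0 because a few patients deteriorate severely. If 6.25% of patients worsen by 16 points, the mean shifts by 0.0625 × 16 = 1.0, but this component alone has an SD of 16 × √(0.0625 × 0.9375) = 3.9, against the protocol's 1.5. The documents give no basis for such a tail, so nothing here rests on it.

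Lastly, the lack of adjustment for baseline NIHSS is not an error, because the endpoint is already a change score. The reference to postoperative scores in the test clause is loose wording, since the interval clause of the same sentence refers to change.

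**Conclusion.** The point holds in this form: the only NIHSS test named is a two-sided test of difference, the planned 95% interval is not tied to ±1, and the normality check will probably move the analysis to a test that does not concern the mean difference on which the margin is defined. At the protocol's planning values, about seven trials in ten (69.3%) would show a significant difference together with an interval inside the margin, with no rule on which governs. The share falls to about 31% at a true difference of 0.25 and 5% at 0. These figures assume an approximately normal mean difference, SD 1.5 and 160 analysed per group; the expectation about the normality check assumes rounded-normal scores. Because the gap concerns the primary conclusion, it should be closed before the data are analysed.

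**What to change.** In the Statistical analysis plan section:

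1. State that the primary analysis is the between-group difference in mean NIHSS change from baseline to the first postoperative assessment, and that equivalence is concluded only if its two-sided 95% confidence interval lies wholly within −1 to +1.
2. Name one mean-based method in advance, with a robust or bootstrap interval to allow for skewed integer scores. Adjustment for the baseline NIHSS already collected is an optional gain in precision.
3. Drop the normality check for the primary endpoint.
4. Label any t-test or Mann-Whitney p-value as supportive only, with no bearing on the equivalence decision.

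The cost is wording. No new data are needed, and under the protocol's inputs the 160 per group gives 84.6% power under this rule, above the 80% target.

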**Methods:**

This is a prospective, single-center, randomized parallel arm equivalent clinical trial, which is approved by China Ethics Committee of Registering Clinical Trials (ChiECRCT-20,160,051). Patients with supratentorial gliomas diagnosed by magnetic resonance imaging will be eligible for the trial. Written informed consent will be obtained before randomly assigning each subject to either the sevoflurane-remifentanil or propofol-remifentanil group for anesthesia maintenance to achieve an equal-desired depth of anesthesia. Intraoperative intervention and monitoring will follow a standard anesthetic management protocol. All of the physiological parameters and other medications administered during the intervention will be recorded. The primary outcome will be neurologic function change assessed by National Institute of Health Stroke Scale (NIHSS) within 4 h after general anesthesia when observer’s assessment of alertness/sedation (OAA/S) reaches 4. Secondary outcomes will include NIHSS and modified NIHSS change 1 and 2 days after general anesthesia, hemodynamic stability, intraoperative brain relaxation, quality of anesthesia emergence, quality of anesthesia recovery, postoperative cognitive function, postoperative pain, postoperative neurologic complications, as well as perioperative medical expense.

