### Discontinuation criteria

#### Massive hemorrhage or massive transfusion

Massive intraoperative bleeding can occur, and this study defines massive bleeding as blood loss exceeding the entire blood volume within 24 h from the start of operation or 50% of circulating blood volume loss within 3 h during operation requiring emergency intervention. Intraoperative massive transfusion (transfusion of more than 10 units of packed red blood cells) may be needed if massive hemorrhage is encountered. If bleeding occurs to this extent and meets either or both of the above criteria, the trial will be discontinued for this particular patient.

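### Intention-to-treat is the only efficacy set in an equivalence trial; a per-protocol set defined by treatment received should stand beside it

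*Protocol article*

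**What the plan says.** The Trial design section describes the study as "open label, randomized parallel arm equivalent clinical trial". The Study purpose section states the hypothesis as a difference in NIHSS change between -1 and 1, and the Sample size calculation section says "1.0 was set as the equivalent margin based on clinical significance".

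The Statistical analysis plan section fixes the population: "All data will be analyzed according to an intent-to-treat", and "all randomized patients originally allocated to the propofol or sevoflurane anesthesia arm at the time of randomization will be used for efficacy analysis". No per-protocol or as-treated set appears anywhere in the article. The same section gives a 95% confidence interval for the difference and a two-tailed type I error of 0.05.

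On missing outcomes it gives two statements: "Missing data will be adjusted using inverse probability weighting and worst-case imputation scenarios" and, later, "Worst observation carried forward method will be used to handle missing data".

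The Discontinuation criteria remove some patients after randomisation. For massive bleeding, "the trial will be discontinued for this particular patient". Similar rules cover anaphylaxis severe enough to stop the operation, venous air embolism and postoperative coma. Under the intention-to-treat statement these patients stay in the efficacy analysis.

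**The concern.** In a superiority trial, intention-to-treat is usually the cautious choice, because departures from allocated treatment work against the claim. In an equivalence trial they usually work for it. If some patients in one arm are maintained partly or wholly on the other agent, or the allocated regimen is not followed, the two groups become more alike and the estimated difference moves toward zero. An interval inside ±1 could then reflect a diluted contrast as well as truly similar agents.

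With one set prespecified, a reader of the results has no planned analysis that separates these explanations. A per-protocol set defined after the data are seen would be open to the charge of selection.

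**Working it through.** **Inputs from the protocol.** Margin 1.0, assumed true difference 0.5, SD 1.5, 160 per group for 80% power, raised to 176 per group for 10% drop-out (Sample size calculation); 95% confidence interval (Statistical analysis plan). I assume that equivalence is declared when that interval lies wholly inside ±1.

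**The plan's own figure.** For two one-sided tests on means, n per group = 2 × SD² × (z₁₋α + z₀.₈₀)² / (margin - difference)² = 18 × (z₁₋α + 0.842)².
- One-sided 0.025: 18 × (1.960 + 0.842)² = 141.3, so 142.
- One-sided 0.05: 18 × (1.645 + 0.842)² = 111.3, so 112.

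Neither gives 160. That is a separate matter and does not affect this point, which uses the enrolled 176 per group.

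**Dilution.** SE = 1.5 × √(2/176) = 0.1599. If the true on-treatment difference is exactly 1.0 (not equivalent) and a share x of the contrast is lost, the intention-to-treat difference is 1 - x. The chance that the upper limit falls below 1 is Φ(x/SE - 1.96); the lower limit plays no practical part.

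| Share of contrast lost (assumed) | x/SE - 1.96 | False equivalence |
|---|---|---|
| 0% | -1.960 | 2.5% |
| 2.5% | -1.804 | 3.6% |
| 5% | -1.647 | 5.0% |
| 10% | -1.335 | 9.1% |
| 15% | -1.022 | 15.3% |
| 20% | -0.709 | 23.9% |

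The effect is smaller when the truth lies further outside the margin. At a true difference of 1.2, 10% dilution leaves 1.08 and a risk of 0.7%; 20% leaves 0.96 and 4.4%.

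**Imputed values.** These were examined by simulating 40,000 trials with 176 per group, a true difference of 1.0, values missing at random and one common imputed change score.
- 10% missing in each arm: the mean difference shrinks to about 0.90. The risk is 9.7% when the imputed change is 0, 8.4% at +3, 6.5% at +5 and 4.6% at +10.
- 5% against 10% missing, imputed +3 to +10: the risk is 0.06% to 1.2% if the worse arm loses more patients, and 21% to 41% if the better arm does.
- Imputed +42: the risk is 0%, because the variance widens the interval.

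So imputation has no fixed direction.

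**Power with a second set.** Take 144 per group, which is 160 less 10% (32 of the 176, or 18%, left out). SE = 1.5 × √(2/144) = 0.1768, and power at a true difference of 0.5 is Φ(0.5/0.1768 - 1.96) = Φ(0.868) = 81%. For all 176 it is Φ(0.5/0.1599 - 1.96) = Φ(1.167) = 88%. If both must pass, the same difference of 0.5 holds in both sets, and the two estimates correlate at √(144/176) = 0.905, the joint normal probability is about 79%.

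**The case against.** **Deviation may be rare.** Allocation is revealed only in the operating room, the maintenance agent is given in a single session, and Table 2 adjusts the allocated agent without switching it. The protocol itself calls anaphylaxis and significant air embolism rare. The 10% drop-out allowance is not a crossover rate. This stands: the dilution shares above are assumptions, and the true figure may be near zero.

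**The interval has some reserve.** A 95% interval tests each side at 2.5%, so 5% dilution only brings the risk to the 0.05 that the plan states. This also stands; the risk passes that level only beyond about 5% dilution, in the least favourable case of a true difference at the margin.

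**A per-protocol set is biased too.** It excludes patients after randomisation. True, and the reason it should accompany intention-to-treat and not replace it.

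**The article condenses a fuller document.** Supportive sets are often left to a separate analysis plan, and no sentence here rules one out. But the section does make a choice, for all data and for efficacy, and it is the choice usual for superiority.

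**Two stronger readings are not supported.** A reader might infer that imputation under this plan always pulls the arms together. It does not: worst observation carried forward uses each patient's own observations, not a common value, and the simulation shows either direction. A reader might also infer that the equivalence claim could not be checked at all. The plan records reasons for discontinuation and the drugs given, and it names weighting and worst-case scenarios for missing data. What is absent is a prespecified analysis by treatment received.

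**Conclusion.** The point holds as a gap in the stated analysis choice: an equivalence claim would rest on one set, in which departures from allocated treatment tend to favour that claim. It does not show that the trial will reach a false conclusion. The figures of 5.0%, 9.1% and 15.3%, against 2.5% without dilution, rest on assumed losses of contrast, on SD 1.5 and on a true difference exactly at the margin. For imputed values the direction depends on how missingness falls between the arms and on the values used. The change should be made, because it is cheap and must be fixed before the data are seen to be credible.

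**What to change.** In the Statistical analysis plan section, keep intention-to-treat and add a per-protocol set defined by treatment received: randomised patients maintained only on the allocated agent, without major eligibility or protocol violations. Propofol at induction is given in both arms and should not count as a deviation.

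Do not define the set by reaching OAA/S 4 within 4 h. That happens after randomisation and the anaesthetic may affect it; dropping slow-emerging or comatose patients could itself hide a difference. For the same reason, exclusion criterion 6 in Table 1 (prolonged emergence, postoperative ventilation) should not be used to remove patients from the set.

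Report the same 95% confidence interval against ±1 in both sets. Describe equivalence as robust only if both intervals lie within ±1; if they disagree, report equivalence as not confirmed. List the deviations by arm, so that the possible dilution can be judged from actual counts.

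The cost is a few sentences and one extra run on data already collected. Power is slightly lower, as shown above, and the per-protocol set lacks the full protection of randomisation.
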